## Mortality and disease severity

Mortality at end of study follow up will be a further secondary endpoint of the study. To ensure patients lost to follow up have not died, cross checking with Australian death registries will occur. Other clinically relevant indicators of liver disease severity MELD and Child Pugh score, will also be monitored at baseline, study end and 3-monthly during the trial period.

## Quality of care indicators

Quality of care indicators, as outlined in the Aims section, will be measured. These indicators are recognized quality indicators ([44](#_ENREF_44)) and highly relevant process measures of successful implementation and effectiveness of the intervention. Attendances will include all planned outpatient medical, allied health, radiology and endoscopy appointments.

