## Secondary Objectives

- To evaluate incremental cost effectiveness for this intervention, relative to usual care. Assessment of quality of life will be a necessary component of the economic analysis. The QALY will be used to assess this outcome.
- To evaluate the effect of CDM on mortality
- To evaluate the effect of CDM on the quality of care provided to patients in the intervention arm. This will be assessed using the following measures:
  - attendance at planned outpatient care;
  - medication adherence;
  - adherence to antibiotic prophylaxis protocols for patients with ascites;
  - adherence to variceal bleeding prevention protocols;
  - adherence and response to alcohol abuse treatment protocols in alcoholic liver disease patients; and
  - referral rates to liver transplantation assessment teams.
- To compare self-management ability and knowledge of patients in the CDM arm with usual care models.

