## Control/usual care group

Control/usual care patients will continue hospital and out of hospital management via usual care processes. To prevent contamination of usual care patients by the intervention, usual care patients will have no contact with CLD nurses until a final end of study interview. Usual care patients will be mailed surveys at baseline, 3 months, 6 months, and then 6-monthly until the end of the trial (24 months after the first patient randomised). At the end of the trial, control group participants are invited for a face-to-face review to complete the surveys, are given the Cirrhosis Booklet and offered an education session.

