## Outpatient review by Specialist Gastroenterologist/Hepatologist

Review by a specialist must be scheduled within 1 month (4 weeks) of discharge from hospital for all patients in the intervention group. The nurse must attend this appointment with the patient. In preparation for the outpatient appointment the following should be updated:

- - Medication list
  - Care Plan
  - Ensure screening and surveillance requirements are up to date (or booked)

At this appointment the specialist will discuss the care plan with the nurse and the patient and sign off on the care plan.

## Month 3, Month 6, Month 12, Month 18

Patients in the intervention group have their Child Pugh and Meld scores completed at 3, 6, 12, 18 months and at end of trial (Appendix N). Collect the information from the most recent bloods taken as part of usual care, the patient will not be required to have a blood test taken just for this score to be done.

Surveys are due for both groups at this time. For intervention patients this should ideally be scheduled at the same time the specialist outpatient appointment is scheduled to enable accurate determination of the Child Pugh and MELD score. Ensure the contact log is up to date. Patients will be provided the option of receiving the surveys via standard post or electronically, via email, at consent.

Record hospital and liver-related outpatient admissions/attendances/non attendances at the month 12 visit.

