## Statistical methods

All analyses will be performed according to an intention-to-treat protocol. Differences between groups for hospitalization rates, quality indicators, satisfaction rates and self-management scores will be assessed using negative binomial regression, which is appropriate for count data with evidence of over-dispersion. All models will allow adjustment for baseline values and other co-variates. Suitable transformations will be applied in the case of non-normally distributed data.

For the economic analysis mean costs between the intervention and control groups will be compared and incremental cost effectiveness ratios presented with confidence intervals. Cost effectiveness acceptability curves for varying threshold values of cost effectiveness will also be presented ([46](#_ENREF_46)). An assessment of the sensitivity of the results obtained to variation in measured resource use, effectiveness and/or unit costs will be undertaken using appropriate one-way and multi-way sensitivity analysis ([47](#_ENREF_47)). Differences between groups in quality of life scores will be assessed using mixed effects regression to account for the repeated measures (every 3 months) and subsequent within-Participant correlation. Survival analysis will be performed using Cox regression with results presented as Kaplan-Meir survival curves.

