| Ascites & HE assessment |  |  |  |  |  |  |  |  |  |  |  |  |  |  |  |  |  | X |
| HCC assessment |  |  |  |  |  |  |  |  |  |  |  |  |  |  |  |  |  | X |
| Osteoporosis assessment |  |  |  |  |  |  |  |  |  |  |  |  |  |  |  |  |  | X |
| Variceal assessment |  |  |  |  |  |  |  |  |  |  |  |  |  |  |  |  |  | X |
| Nutrition assessment |  |  |  |  |  |  |  |  |  |  |  |  |  |  |  |  |  | X |
| End of study outcome |  |  |  |  |  |  |  |  |  |  |  |  |  |  |  |  |  | X |
| Interview for selected pts |  |  |  |  |  |  |  |  |  |  |  |  |  |  |  |  |  | X |

| Activity Schedule for INTERVENTION patients |  | Treatment Period  Day 7 to Week 11 are scheduled from the discharge date from hospital.  From Month 3 visits are scheduled from randomisation. | | | | | | | | | | | | | | | |
| --- | --- | --- | --- | --- | --- | --- | --- | --- | --- | --- | --- | --- | --- | --- | --- | --- | --- |
|  | Baseline | Day 7 | Day 14 | Week  3 | Week  4 | Week  5 | Week  6 | Week  7 | Week  8 | Week  9 | Week  10 | Week  11 | Month  3 | Month  6 | Month  **12** | Month  18 | Month 24/EOS |
| Informed Consent | X |  |  |  |  |  |  |  |  |  |  |  |  |  |  |  |  |
| Child Pugh / MELD | X |  |  |  |  |  |  |  |  |  |  |  | X | X | X | X | X |
| SURVEYS (5) | X |  |  |  |  |  |  |  |  |  |  |  | X | X | X | X | X |
| Concomitant Medications | X |  |  |  |  |  |  |  |  |  |  |  |  |  |  |  | X |
| Comorbidities list | X |  |  |  |  |  |  |  |  |  |  |  |  |  |  |  | X |
| Charlson Comorbidity Index | X |  |  |  |  |  |  |  |  |  |  |  |  |  |  |  |  |
| Randomisation | X |  |  |  |  |  |  |  |  |  |  |  |  |  |  |  |  |
| Carer and GP assessment | X |  |  |  |  |  |  |  |  |  |  |  |  |  |  |  |  |
| GP communication^a^ | X | X |  |  | X |  |  |  |  |  |  |  |  |  |  |  |  |
| Face to Face Contact | X | X |  |  | X |  |  |  |  |  |  |  | X | X | X | X | X |
| Telephone Contact^b^ |  |  | X | X | X | X | X | X | X | X | X | X |  |  |  |  |  |
| Hepatologist OPD |  |  |  |  |  |  |  |  |  |  |  |  | X | X | X | X | X |
| Care Plan review^c^ | X | X |  |  | X |  |  |  |  |  |  |  | X | X | X | X | X |
| Alcohol Use assessment | X |  |  |  |  |  |  |  |  |  |  |  |  |  |  |  | X |
| Ascites & HE assessment | X |  |  |  |  |  |  |  |  |  |  |  |  |  |  |  | X |
| HCC assessment | X |  |  |  |  |  |  |  |  |  |  |  |  |  |  |  | X |
| Osteoporosis assessment | X |  |  |  |  |  |  |  |  |  |  |  |  |  |  |  | X |
|  |  |  |  |  |  |  |  |  |  |  |  |  |  |  |  |  |  |

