## Appendix K – Outpatient Attendance Log

Date of randomisation: ___ / ___ / ____

Period of review (tick only one):

Randomisation Date ___ / ___ / ____ to 12 months ___ / ___ / ____

12 months ___ / ___ / ____to trial end ___ / ___ / ____

| Outpatient review 1 |
| --- |
| Appointment Date ___ / ___ / ____  Attended? Yes  No  If no Why? Did not turn up  Cancelled |
| Outpatient review 2 |
| Appointment Date ___ / ___ / ____  Attended? Yes  No  If no Why? Did not turn up  Cancelled |
| Outpatient review 3 |
| Appointment Date ___ / ___ / ____  Attended? Yes  No  If no Why? Did not turn up  Cancelled |
| Outpatient review 4 |
| Appointment Date ___ / ___ / ____  Attended? Yes  No  If no Why? Did not turn up  Cancelled |
| Outpatient review 5 |
| Appointment Date ___ / ___ / ____  Attended? Yes  No  If no Why? Did not turn up  Cancelled |
| Outpatient review 6 |
| Appointment Date ___ / ___ / ____  Attended? Yes  No  If no Why? Did not turn up  Cancelled |

| Outpatient review 7 |
| --- |
| Appointment Date ___ / ___ / ____  Attended? Yes  No  If no Why? Did not turn up  Cancelled |
| Outpatient review 8 |
| Appointment Date ___ / ___ / ____  Attended? Yes  No  If no Why? Did not turn up  Cancelled |
| Outpatient review 9 |
| Appointment Date ___ / ___ / ____  Attended? Yes  No  If no Why? Did not turn up  Cancelled |
| Outpatient review 10 |
| Appointment Date ___ / ___ / ____  Attended? Yes  No  If no Why? Did not turn up  Cancelled |
| Outpatient review 11 |
| Appointment Date ___ / ___ / ____  Attended? Yes  No  If no Why? Did not turn up  Cancelled |
| Outpatient review 12 |
| Appointment Date ___ / ___ / ____  Attended? Yes  No  If no Why? Did not turn up  Cancelled |
| Outpatient review 13 |
| Appointment Date ___ / ___ / ____  Attended? Yes  No  If no Why? Did not turn up  Cancelled |

If more than 13 appointments in 12 months, please print this page a second time.

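### Read as a count, the outpatient-attendance indicator can favour the intervention through the trial's own visit schedule; it needs planned appointments as its denominator

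*Protocol*

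**What the plan says.** The Secondary Objectives list "attendance at planned outpatient care" first among the measures of quality of care. The Outcomes section (Quality of care indicators) sets the scope: "Attendances will include all planned outpatient medical, allied health, radiology and endoscopy appointments". Visits that the trial itself requires are not excluded.

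The Statistical methods section names the model: "Differences between groups for hospitalization rates, quality indicators, satisfaction rates and self-management scores will be assessed using negative binomial regression". It justifies this model as suited to over-dispersed counts. It gives no denominator or offset for the number of appointments planned.

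The trial adds specialist visits in one arm:

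- Outpatient review section: "Review by a specialist must be scheduled within 1 month (4 weeks) of discharge from hospital for all patients in the intervention group", and "The nurse must attend this appointment with the patient".
- Activity Schedule for INTERVENTION patients: the row "Hepatologist OPD" is marked at Months 3, 6, 12, 18 and 24/EOS.
- Activity Schedule for CONTROL patients: there is no such row. The text on that arm reads: "Control/usual care patients will continue hospital and out of hospital management via usual care processes".

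Appendix K logs, for each appointment, the date, whether it was attended and, for a missed one, the reason ("If no Why? Did not turn up" or cancelled). It has no field for the type of appointment or for whether the trial scheduled it.

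**The concern.** An intervention patient is given up to six specialist appointments that a control patient is not given by the trial. If the endpoint is the number of attendances, those appointments enter it in one arm only. The count can then rise although each patient keeps the same share of appointments as before.

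The objective is to judge whether the care model improves quality of care, and attendance at planned care is one of the measures. Two explanations would be mixed in one number: patients were offered more visits, or patients kept more of those they were offered. The Background reports improved outpatient attendance as a significant finding of the pilot, so this result is likely to be cited. The primary outcome (unplanned liver-related admissions), mortality and the cost analysis are not affected.

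**Working it through.** The protocol gives no target figure for this indicator, so there is nothing to reproduce. The check is how far the count moves when attendance behaviour is held equal.

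**Inputs from the protocol**

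- Trial-fixed specialist reviews, intervention: 1 (within four weeks, in the text) + 5 (Months 3, 6, 12, 18, 24/EOS, in the schedule) = 6. Control: 0.
- Arm size 75 (Randomization, stratification, blinding). Attrition 20% (Sample size and power analysis), so 75 × 0.8 = 60.
- Significance level 0.05.

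**Assumptions (not in the protocol)**

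- Probability *p* = 0.75 of attending any planned appointment, the same in both arms and for all appointment types.
- *c* = 12 appointments planned per control patient over 24 months; *t* planned per intervention patient.
- Two-sided test; negative binomial dispersion *k* = 0, 0.3 or 1.0.

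**Step 1: ratio of counts.** Expected attendances are *p·c* and *p·t*, so the ratio is *t/c*; *p* cancels.

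- All six fixed reviews replace usual visits: 12/12 = 1.00.
- Six specialist reviews against four in usual care, plus eight other appointments in each arm: (6 + 8)/(4 + 8) = 14/12 = 1.17.
- All six are additional: (12 + 6)/12 = 1.50.

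If all six are additional but *c* differs, (*c* + 6)/*c* is 2.50 at *c* = 4, 1.75 at 8, 1.33 at 18 and 1.23 at 26. The last is two full Appendix K logs of 13 appointments a year.

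**Step 2: chance of a significant result in favour of the intervention.** SE(ln ratio) = √[(1/μ_c + k)/n + (1/μ_t + k)/n], and chance = Φ(ln ratio / SE − 1.96).

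Example, 14 against 12, *k* = 0.3, *n* = 75: μ_c = 9.0 and μ_t = 10.5. SE = √[(0.1111 + 0.3 + 0.0952 + 0.3)/75] = 0.1037. ln(14/12) = 0.1542. Chance = Φ(1.487 − 1.96) = 0.32.

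| Planned, intervention v control | Ratio of counts | *k* = 0 | *k* = 0.3 | *k* = 1.0 |
|---|---|---|---|---|
| 12 v 12 | 1.00 | 2.5% (nominal) | 2.5% | 2.5% |
| 14 v 12 | 1.17 | 75–84% | 26–32% | 12–14% |
| 18 v 12 | 1.50 | over 99% | 94–98% | 57–66% |

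Ranges run from 60 to 75 patients per arm.

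**Step 3: attended out of planned.** *p·t/t* = *p·c/c* = 0.75 in both arms, a ratio of 1.00 in every row. A negative binomial model with log planned appointments as offset gives the same.

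**Step 4: the reverse case.** With 18 against 12 planned and controls attending 75%, the intervention count stays higher until attendance per appointment falls below 0.75 × 12/18 = 0.50. A count could therefore show a gain while patients attend worse.

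**The case against.** **The protocol never says that the indicator is a raw count.** This stands. The sentence on attendances can be read as setting which appointment types belong, and recording missed and cancelled visits would be pointless for a bare count. The model sentence is broad: it also covers satisfaction rates and self-management scores, which are not event counts. A negative binomial model with planned appointments as offset would fit it. A reader might infer that the protocol commits to a raw count; the text does not go that far. It does assign a model for counts to an indicator whose scope takes in the trial's own visits, and it names no denominator. Anyone following it as written may produce the confounded result.

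**The denominator belongs in the analysis plan.** Leaving detail to that plan would be no fault. Here the protocol has already chosen both the scope and the model family, and taken together they permit a result that misleads.

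**More specialist contact is the intervention.** This also stands in part. The protocol calls these indicators process measures of implementation as well as effectiveness, and extra reviews are a legitimate sign of delivery. They are not evidence of better attendance, so the two need separate reporting.

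**The inflation may be small or nil.** This stands. Intervention patients see their usual gastroenterologist, so fixed reviews may replace routine visits. A reader might infer from specialist visits alone (six against four, a ratio of 1.5) that a spurious significant gain is close to certain. The indicator also covers allied health, radiology and endoscopy, which dilute the effect: eight such appointments in each arm bring the ratio down to 1.17.

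**Conclusion.** The point holds in a limited form. Taken as a count, the attendance indicator can favour the intervention through scheduling alone, and a difference between arms would not show better attendance at planned care. The count of fixed reviews, six against none, comes from the protocol.

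The size cannot be determined from the protocol. It depends on the unstated number of usual-care appointments and on how many fixed reviews replace usual visits. The plausible span runs from no effect to a ratio of about 1.5 at 12 usual-care appointments, and higher if usual care plans fewer. The chances of significance depend further on the assumed dispersion. The ratio of 1.00 for attended out of planned assumes the same attendance probability for every type of appointment.

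This is one of several quality measures under a secondary objective. It is worth correcting because a better measure is available from data already collected.

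**What to change.** - In Quality of care indicators and in Statistical methods, define the indicator as appointments attended out of appointments planned per patient, from the Attended Yes/No field of Appendix K. State whether a cancelled appointment stays in the denominator.
- Analyse it with a binomial model that allows for within-patient correlation (for example, logistic regression with standard errors clustered by patient), or with negative binomial regression and log planned appointments as offset.
- Keep all planned appointments in both arms in the main comparison. Removing the fixed reviews would drop core specialist visits from one arm while keeping routine liver-clinic visits in the other. An analysis without them is at most a sensitivity analysis, and it would need a field in Appendix K to mark trial-scheduled visits.
- Report the number of specialist reviews planned and attended per arm separately, as delivery of the intervention.
- Reconcile the scope. The indicator covers all planned outpatient appointments, whereas the visit text and activity schedules ask for liver-related ones. The denominator depends on which are logged.

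The cost is analysis wording; visits, care and sample size do not change. The apparent gain in attendance may be smaller.

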## Patient Satisfaction and Self-Management Ability

The following surveys will be administered at baseline, 3 months, 6 months and then 6-monthly and at the end of the trial:

- PIH - The Partners in Health (PIH) scale to assess changes in patient self-management ability ([45](#_ENREF_45)).
- A local disease specific knowledge assessment questionnaire, the “Cirrhosis Knowledge Assessment Questionnaire”.
- The ASK-12, a medication adherence tool will be used to determine medication adherence
- A Satisfaction Survey will be administered at the end of the study in both groups.

Qualitative feedback from patients will also be sought at the end of trial via a telephone interview with a researcher not directly involved in the patient’s care. Although consent for inclusion in the interview will be sought at the start of the trial, patients will be given the chance to ‘opt out’ if they are approached to participate and decide that they do not wish to. After the interview if patients feel they wish to change their answer or review their answer, a number will be provided so they can do so within a certain time.

## Intervention period

Patient recruitment will occur during a 12-18 month window and the intervention will occur for 24 months for each patient. In the case of patient death, liver transplantation and loss to follow up, the study will end.

# Statistical Methods

## Sample size and power analysis

The trial will be powered for the primary endpoint of unplanned liver-related admissions. Assuming an admission rate of three admissions per person per year in the usual care group, and a reduction of 20 % in the treatment group, a sample size of 146 (50 per site) would provide 80% power to detect a significant difference in event rates between groups at a type 1 error rate of α=0.05. This assumes a median follow-up time of 18 months, as well as allowing for a 20% attrition rate throughout the trial. Recruitment of a sample size of 147 patients within 12 months is feasible and represents approximately 38 patients per site. The anticipated caseload of intervention patients per site is 19, which was less than the caseload during the pilot trial (40) and will be feasible with a 0.6 fte RN level 3 nurse at each site.

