# Background

**Cirrhosis and chronic liver failure**

A variety of insults to the liver can lead to progressive fibrosis and cirrhosis. The most common causes in Australia include; alcohol abuse, chronic hepatitis C (HCV) infection, and non-alcoholic fatty liver disease (NAFLD). Ongoing injury to a cirrhotic liver may result in decompensation of liver functions or chronic liver failure (CLD). CLD is manifested by complications such as; ascites, variceal bleeding, encephalopathy, sepsis (most commonly spontaneous bacterial peritonitis) and renal dysfunction, protein calorie malnutrition and hepatocellular carcinoma (HCC). The prognosis following the onset of CLD is poor. Patients with early CLD (Child Pugh class B) have a 2-year survival of only 60% and this falls to 35% in advanced CLD (Child Pugh class C)([1](#_ENREF_1)).

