However, despite the availability of effective therapies, available data suggests the delivery of such care to CLD patients is suboptimal. In routine practice poor rates of variceal screening and prophylaxis of high risk varices ([12](#_ENREF_12)), poor adherence to guidelines for hepatocellular carcinoma surveillance ([13](#_ENREF_13), [14](#_ENREF_14)) and poor adherence to ascites management guidelines ([15](#_ENREF_15)) have been observed by multiple investigators. Suboptimal care is a likely contributor to frequent, prolonged, costly and often preventable readmissions that characterize this disorder ([16](#_ENREF_16)). The CLD-related readmission rates have been identified as 14 %, 37 % and 53 % at 1 week, 3 months and 6 months respectively by recent studies ([16](#_ENREF_16), [17](#_ENREF_17)), with an estimated 52 % of these readmissions judged as preventable by improved care. The reasons for inadequate care delivery in CLD patients appear complex and multi-factorial. The lack of hospital clinician focus on preventative care measures, absence of robust systems to improve patient follow up and monitoring following discharge, and poor integration of hospital and primary care team members are all likely contributing factors. Finally, poor engagement of patients in their own care and inadequate patient education is also likely to be of major importance.

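### The stated 80% power at N = 146 does not follow from the protocol's own inputs: at 18 months it is 67–77% before any over-dispersion, and no dispersion is stated

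*Protocol*

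**What the plan says.** The Protocol section Sample size and power analysis takes as its control rate "an admission rate of three admissions per person per year in the usual care group". The effect it is designed for is "a reduction of 20 % in the treatment group". With α set to 0.05, its conclusion is that "a sample size of 146 (50 per site) would provide 80% power to detect a significant difference in event rates between groups". On exposure it adds: "This assumes a median follow-up time of 18 months, as well as allowing for a 20% attrition rate throughout the trial". It does not state sidedness, a formula or a dispersion parameter.

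The same paragraph then gives 147 patients at roughly 38 per site. Participant Population names 4 sites. Number of Participants aims for 150 and permits up to 200. Intervention period plans 24 months for each patient.

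Under Statistical methods, hospitalization rates are to be analysed by "negative binomial regression, which is appropriate for count data with evidence of over-dispersion".

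**The concern.** Two things do not fit. First, an 80% claim for a 20% rate reduction with 146 patients looks too favourable for 18 months of follow-up and 20% attrition, even with the smallest variance a count model allows. Second, the stated N leaves no visible room for over-dispersion, although the model chosen for the primary endpoint is justified by it.

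The background presents the trial as adequately powered and able to give definitive evidence on this model of care. If real power is well below 80%, a null result would be read as evidence against a 20% reduction that the trial had a limited chance of detecting. The error does not bias the estimated rate ratio or its interval.

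**Working it through.** **Inputs.** From Sample size and power analysis: control rate 3 per person-year; rate ratio 0.80, so 2.4 per person-year; α = 0.05; power 80%; follow-up t = 1.5 years; attrition 20%. From Trial design: 1:1 allocation. Assumptions made here: a two-sided test, and the 18-month median used as the average follow-up.

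**Formulas** (log rate ratio, Wald). With m₀ = 3t, m₁ = 2.4t and k the negative binomial dispersion (k = 0 is Poisson):

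- n per arm = (1.96 + 0.8416)² × (1/m₀ + 1/m₁ + 2k) / (ln 0.8)², where (1.96 + 0.8416)² = 7.849 and (ln 0.8)² = 0.04979
- power = Φ(0.2231/SE − 1.96), where SE = √[(1/m₀ + 1/m₁ + 2k)/n]

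**Step 1: what reproduces the stated N.** Take t = 2 and k = 0. Then 1/6 + 1/4.8 = 0.375 and n = 7.849 × 0.375/0.04979 = 59.1 per arm, or 118.2 in total. Dividing by 0.8 gives 147.8. Rate-difference, null-variance and square-root versions give 147–148. Power at 146 with 20% lost (58.4 per arm) has SE = √(0.375/58.4) = 0.0801, so Φ(0.825) = 79.5%. The stated figure fits 24 months, not 18.

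**Step 2: the stated inputs.** Take t = 1.5 and k = 0. Then 1/4.5 + 1/3.6 = 0.500 and n = 78.8 per arm, or 157.6 in total (158). Dividing by 0.8 gives 197. The other Poisson versions give 196–198; inflating by 1.2 instead of dividing by 0.8 gives 188–190.

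**Step 3: power at N = 146 and 18 months, Poisson.**

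- The 20% contribute nothing: n = 58.4, SE = 0.0925, Φ(0.452) = 67%.
- They contribute half their time: n = 65.7, power 72.5%.
- The 18 months already absorbs attrition: n = 73, SE = 0.0828, Φ(0.736) = 77%.

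Put another way, Poisson power of 80% needs 157.6 × 1.5 = 236.4 person-years. That is 236.4/146 = 1.62 years, or about 19.4 months for each randomised patient. The Step 1 reading supplies 24 × 0.8 = 19.2 months. The stated inputs supply 18 months at most, and 18 × 0.8 = 14.4 if attrition is additional and complete.

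**Step 4: over-dispersion.** The protocol gives no k, so the values below are assumptions. Power at N = 146:

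| k (assumed) | 18 months, 20% full loss | 18 months, no further loss | 24 months, 20% full loss |
|---|---|---|---|
| 0 | 67% | 77% | 79.5% |
| 0.1 | 53% | 63% | 61% |
| 0.25 | 40% | 48% | 45% |
| 0.5 | 29% | 34% | 31% |

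As an example, k = 0.25 with 58.4 per arm at 18 months gives SE = √[(0.5 + 0.5)/58.4] = 0.1309 and Φ(−0.255) = 40%.

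**Step 5: the permitted N = 200, 18 months, 20% full loss** (80 per arm): 81% at k = 0, 66% at k = 0.1, 51% at k = 0.25 and 37% at k = 0.5.

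**Step 6: the site figures.** 4 × 50 = 200, not 146; 4 × 38 = 152. The 197 from Step 2 is close to 200, but nothing in the text shows that this is where 50 per site came from.

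**The case against.** **The shortfall may be one stale input.** Intervention period plans 24 months per patient and the target is 150. The Poisson calculation needs 118.2 retained patients at 24 months, and 150 × 0.8 = 120. On those inputs the 80% claim holds without over-dispersion. This stands as an explanation of the error. It does not make the written paragraph right, since that paragraph says 18 months, and it leaves over-dispersion unaddressed.

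**The 67% is not a ceiling.** A reader might infer that power is 67% at best. That requires the 20% to contribute no person-time on top of 18 months, whereas a rate model uses each patient's time up to death or loss. The background says: "Patients with early CLD (Child Pugh class B) have a 2-year survival of only 60% and this falls to 35% in advanced CLD". Under exponential survival, 60% and 35% at 2 years give mean follow-up of 18.8 and 14.9 months within a 24-month plan, so 18 months may already include much of the mortality, at least for Child Pugh B. The objection stands, and the range is therefore 67–77%. The same survival figures also show that 24 months with only 20% loss needs justification.

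**Power below 40% is not established.** A reader might infer that power is probably under 40%. At 18 months that needs k above about 0.25 (20% full loss) or 0.37 (no loss), and the protocol gives no k. The pilot interval in the background is for bed days, so it cannot supply a dispersion for admission counts.

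**The cited readmission figures do not settle the rate or the dispersion.** The background reports: "The CLD-related readmission rates have been identified as 14 %, 37 % and 53 % at 1 week, 3 months and 6 months respectively". At a constant 3 per year, Poisson counts would imply 53% readmitted by 3 months and 78% by 6 months, so it is tempting to conclude that the true rate is lower or that k is large. The documents do not support this. For any k ≥ 0, a constant mean rate of 3 per year gives at most 1 − exp(−3 × 7/365) = 5.6% readmitted in the first week, yet the same sentence reports 14%. The constant-rate model fails on the data it would be fitted to. Those data are also proportions from outside cohorts in two studies.

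**Sidedness is unstated.** One-sided calculations at 18 months come close: 148–149 with inflation by 1.2, or 81.9% power at 146 with half the time lost. Nothing in the protocol announces a one-sided test, and its reference to a significant difference between groups reads as two-sided.

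**Conclusion.** Wrong as written. With a two-sided test and 18 months taken as the average follow-up, N = 146 gives 67–77% power under Poisson variance, depending on how attrition is read. The stated 80% would need about 197 patients if the 20% are fully lost, or 158 if attrition is already in the 18 months. The stated N matches a two-sided 24-month calculation with 20% loss and no over-dispersion. That source is an inference, because the protocol shows no formula.

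Every calculation found that reaches about 146 uses zero dispersion, which conflicts with the reason given for the negative binomial model. The direction is certain, since any k > 0 lowers power. The size is not: it rests on assumed k, and moving to 24 months does not restore 80% even at k = 0.1 (61%). Because the protocol gives a median and not a mean, the Poisson figures would reach 80% only if mean exposure were about 19.4 months per randomised patient. The protocol does not say this.

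**What to change.** Rewrite the power paragraph so that it:

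- uses the planned negative binomial model with a stated dispersion and its source, for example the pilot's admission counts;
- states the sidedness of the test;
- uses one follow-up assumption, reconciling the 18 months in Sample size and power analysis with the 24 months in Intervention period;
- says how attrition, including death, reduces person-time, so that it is counted once;
- reports power and the minimum detectable rate ratio for 150 and for the permitted 200 patients, over a range of dispersion values;
- withdraws the 80% claim for 146 if 18 months is kept;
- reconciles 146, 147, 50 per site (200 at 4 sites) and about 38 per site.

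The cost is one paragraph and a less favourable stated power. No extra patients and no change to the design are required.
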